### Statistical methods

To evaluate potential effects of heat exposure and the heat adaptation strategy on fetal and maternal physiological responses, behavioral adaptations, and pregnancy outcomes, a multi-level analytical framework will be employed. Descriptive analyses will summarize each study variable, presenting measures of central tendency (e.g., mean, median) and variability (e.g., standard deviation, interquartile range) for continuous variables, and absolute and relative frequencies for categorical variables. Subgroup comparisons by intervention status, exposure to heat-risk periods during pregnancy, age group, gestational age, and occupation will be performed to indicate group-specific patterns in heat-related effects.

Both univariable and multivariable analyses will be used to explore preliminary associations between exposure, mediators, and outcomes. For repeated measurements Linear mixed effects models (LMMs) with random intercepts will be fitted (e.g., heart rate, HRV, physical activity), incorporating both time-varying covariates (e.g., WBGT, time of day) and fixed participant-level covariates (e.g., age, BMI, gestational age, parity, occupation). Interaction terms between intervention and heat exposure will be tested to assess potential effect modification. Non-linear extension will be considered if necessary.

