## Methods and analysis

### Study objectives

Physio-HeMAB study has the following objectives:

Primary objective: to assess the effect of heat exposure (with and without the heat adaptation strategy) on (1) maternal heart rate as a proxy for maternal heat strain.

Secondary objectives: to assess the effect of heat exposure (with and without the heat adaptation strategy) on (1) maternal heart rate variability and (2) physiological strain index as further proxies for maternal heat strain, (3) maternal sleep duration, (4) maternal physical activity, and (5) on fetal strain during assessments.

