#### Data collected by sensors

Five sensors will collect data over a seven-day study period for each participant (Table 1: Device specifications).

**Table 1 Tab1:** Device specifications

DEVICE	GENEActiv Original	Bittium Faros™ 180	Calera Research	Hygrometer PCE-WB 20SD	SwitchBot Meter
COMPANY	ActivInsights, United Kingdom	Bittium Biosignals Ltd., Finland	greenTEG AG Switzerland	PCE Instruments UK Ltd., United Kingdom	SWITCHBOT INC, USA
MEASURE-MENT	Three-axial Acceleration, Near body temp., Ambient light	ECG, Acceleration	Estimated CBT, Skin temp., Acceleration	WBGT	Air temp., Humidity
TYPE OF SENSOR	Wearable motion sensor	Biomedical wearable electro-cardiogram	Skin temperature and heat-flux monitor	Environmental heat stress meter	Environmental sensor
RESOLUTION	100 Hz	250 Hz	17 mHz	17 mHz	17 mHz
DATA TRANSFER	Cradle with USB cable	Micro-USB cable	Bluetooth BLE	SSD Card	Mobile Phone Application
DATA FORMAT	BIN	EDF	CSV	CSV	CSV

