**Fig. 3 Fig3:**
[figure not shown]
Study timeline. Seven-day continuous monitoring period with three scheduled clinic visits. Pt = Part, Qs= Questionnaires

Participants are encouraged to continue all components of data collection throughout the seven-day monitoring period, as this will capture more diverse exposure to environmental stressors. However, participants are given the option to terminate the trial on day four, in which case final study procedures will be conducted on day four instead of day seven.

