### Sample size and selection of subjects

The sampling method will be consecutive sampling of women who visit any of the four purposefully selected HDSS health facilities for antenatal consultations. Consideration will be made for pregnant women who can conveniently attend the health facility at least three times during the physiological measurement period. Inclusion criteria are (1) being a pregnant woman in the third trimester (> 28 weeks) with a (2) singleton pregnancy. Further inclusion criteria are (3) being of legal age, (4) able to give consent, (5) registration (having an ANC card) and (6) living within 10 km proximity of one of the four selected HDSS health facilities. Exclusion criteria are (1) illness that requires hospital admission or immediate delivery, (2) known fetal malformations, and 2) a known psychological or mental health concern.

The primary outcome variable is maternal heart rate (beats per minute, bpm), which serves as a physiological proxy for maternal heat strain, reflecting cardiovascular responses to heat exposure. To determine an appropriate sample size for the Physio-HeMAB study, a power analysis was conducted for comparing mean heart rates between two independent groups. Assuming a mean detectable difference of 5 bpm, a common standard deviation of 10 bpm, a two-sided significance level (α) of 0.05, and 80% statistical power, the required sample size is 63 per group. The study will enroll 200 participants in total across the four HDSS health facilities, 100 in the intervention group and 100 in the control group. As this is the first time this type of study will be conducted in this setting, it is not yet possible to precisely estimate potential attrition, data loss and inter-individual variability. Therefore, the sample size is chosen to provide a conservative margin, ensuring that even with 30% attrition, the study retains adequate power to detect clinically relevant differences in heart rate between groups.

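### If hourly or finer wearable data are analysed with random intercepts as the only dependence structure, the standard errors of the heat slope and the intervention-by-heat interaction will be too small

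*Protocol article*

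**What the plan says.** The primary objective (Study objectives) is "to assess the effect of heat exposure (with and without the heat adaptation strategy) on (1) maternal heart rate". The Statistical methods section gives the model for repeated outcomes: "For repeated measurements Linear mixed effects models (LMMs) with random intercepts will be fitted (e.g., heart rate, HRV, physical activity". Its covariates are described in these terms: "incorporating both time-varying covariates (e.g., WBGT, time of day) and fixed participant-level covariates". On the adaptation strategy it says: "Interaction terms between intervention and heat exposure will be tested to assess potential effect modification". The one extension offered is "Non-linear extension will be considered if necessary", which concerns the mean curve and not the covariance.

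The data are dense. Under Data collected by sensors: "Five sensors will collect data over a seven-day study period for each participant". Table 1 gives ECG at 250 Hz and WBGT at 17 mHz, about one reading a minute. The article does not state the epoch to which these signals are reduced, or whether the intercepts belong to women, facilities or clusters.

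The sample size rests on a comparison of two group means: "Assuming a mean detectable difference of 5 bpm, a common standard deviation of 10 bpm".

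**The concern.** A random intercept per woman lets women differ in average heart rate and in nothing else. It implies one heat slope per arm, apart from any fixed interactions, and residuals that are exchangeable within a woman.

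The article gives reasons to doubt both assumptions. The Conceptual framework section expects the impact of heat to differ with maternal characteristics and behaviour, and the sample-size section says inter-individual variability cannot yet be estimated precisely. Heart rates taken close together also share activity, posture and sleep state. A time-of-day covariate removes only the average daily pattern.

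The interaction compares women's slopes between arms. Its precision is therefore limited by the number of women (200 enrolled, 140 after 30% attrition), and in turn by the facilities. A model that counts readings as the information reports intervals that are too narrow and finds effect modification too often. The heat slope and its contrast between arms are the quantities in the primary objective.

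**Working it through.** **1. The plan's own figure.** n per group = 2(1.96 + 0.8416)² × 10² / 5² = 62.8, so 63. This matches. It concerns a simple difference in means between independent women, so the point made here does not touch it. Attrition of 30% leaves 100 × 0.70 = 70 per arm.

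**2. Inputs.** From the article: 70 women per arm, 7 days (168 hours), about one WBGT reading a minute (about 10,080 per woman). Assumed, because the article does not give them:
- residual SD σ = 8 bpm, held at that value for hourly and 5-minute data;
- WBGT with diurnal amplitude 4 °C, day-to-day SD 1.5 °C and short-term SD 1 °C, so var(x) = 4²/2 + 1.5² + 1² = 11.25;
- between-woman SD of the heat slope, τ, from 0 to 1 bpm/°C;
- one-hour residual autocorrelation, ρ, of 0, 0.5 or 0.8.

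**3. Closed form for an omitted random slope (ρ = 0).** With m readings per woman,

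true SE / model SE = √(1 + τ² m var(x) / σ²), and actual error rate = 2[1 − Φ(1.96 / ratio)].

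- Hourly, τ = 0.25: m var(x) = 168 × 11.25 = 1,890. Ratio = √(1 + 0.0625 × 1,890 / 64) = 1.69, so the error rate is about 24%.
- Hourly, τ = 0.1: ratio = √(1 + 0.01 × 1,890 / 64) = 1.14, so about 8.5%. Weak heterogeneity does little harm at this epoch.
- 5-minute, τ = 0.25 (m = 2,016): ratio 4.8.
- 1-minute, τ = 0.25 (m = 10,080): ratio 10.6.

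A fitted mixed model agrees with the first line. In one simulated hourly data set (ρ = 0, τ = 0.25), adding a random WBGT slope raised the interaction SE from 0.032 to 0.052, a ratio of 1.6.

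**4. Simulation under no true interaction.** The model was the random-intercept model in its within-woman limit, adjusted for time of day except for daily means. The entries are the percentage of interaction tests significant at nominal 5%.

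| Epoch | ρ | τ = 0 | τ = 0.25 | τ = 0.5 | τ = 1.0 |
|---|---|---|---|---|---|
| Hourly | 0 | 5 | 27 | 51 | 72 |
| Hourly | 0.5 | 26 | 35 | 59 | 71 |
| Hourly | 0.8 | 36 | 46 | 54 | 75 |
| 5-minute | 0 | 5 | 73 | 85 | not run |
| 5-minute | 0.5 | 75 | 87 | 86 | not run |
| 5-minute | 0.8 | 83 | 89 | 88 | not run |
| Daily mean | 0 | 5 | 12 | 22 | 37 |
| Daily mean | 0.5 | 6 | 8 | 11 | 19 |
| Daily mean | 0.8 | 5 | 5 | 7 | 14 |

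The 5-minute rates carry about ±4 to 9 points of Monte Carlo error. The heat slope behaves similarly: hourly, it is rejected 15% of the time at (ρ, τ) = (0, 0.25), 22% at (0.5, 0) and 45% at (0.5, 0.5). For the interaction, true SE over model SE is about 1.7 to 5.6 hourly and 4 to 12 at 5 minutes when either feature is present. For daily means it is 1.0 to 2.1.

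**5. Do woman-level methods repair it?** With standard errors robust at the level of the woman, the interaction's rejection rate changes as follows:
- hourly, (0.5, 0.25): 36% to 5%;
- hourly, (0.8, 0.5): 58% to 7%;
- 5-minute, (0.5, 0.25): 79% to 4%.

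A t-test on per-woman slopes gave 4% to 7% in a separate hourly simulation.

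**6. What they do not repair.** Step 5 has no variation in the heat slope between facilities. Take hourly data with τ = 0.25, ρ = 0 and two facilities per arm. The woman-level variance of the slope contrast is 2(0.0625 + 64/1,890)/70 = 0.00275. A facility slope SD of φ adds 2φ²/2 = φ². At φ = 0.05 the SE ratio is √(1 + 0.0025/0.00275) = 1.38, and at φ = 0.10 it is √(1 + 0.01/0.00275) = 2.15. The per-woman t-test then rejects a true null about 15% and 35% of the time, and about 59% at φ = 0.20. These φ values are also assumptions.

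Facility-by-heat fixed effects are no remedy. Facilities are nested in arms, so four facility-by-heat columns plus one arm-by-heat column have rank 4. The interaction is aliased.

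**The case against.** The strongest reply is that this is a short statistics section in a journal article. It nowhere says that random intercepts are the only dependence structure, and it speaks of a multi-level framework. Slope structure, residual covariance and epoch may be set out in a full protocol or analysis plan that is not shown. That stands, and it is why the point is conditional. A reader might infer that the plan rules out random slopes or robust variance, but the text does not say so. What remains is that the article does state a random-effects structure and a test built on it. A team that fits exactly that to hourly data will get the problem shown.

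Second, the size is not in the documents. Device logging rates are not analysis epochs, and τ, ρ, σ and the WBGT variation are all assumed. That also stands. A flat claim of heavily inflated error is not supported, because the range starts at no inflation. Nor are the simulated data complete to the plan's own terms: every woman contributes 168 hours, whereas "participants are given the option to terminate the trial on day four", and WBGT is logged at home only where feasible.

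Third, the article presents these regressions as exploring preliminary associations. No decision rule hangs on the interaction, and the only powered comparison is the difference in mean heart rate. This limits the stakes: a reader might infer that the trial's confirmatory test is invalid, and the article does not support that. It does not remove the point, since the primary objective is about the heat effect with and without the strategy, and exploratory intervals should still have roughly their stated coverage.

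**Conclusion.** The concern holds in conditional form. As written, the model omits two ordinary features of such data. If hourly or finer readings are analysed and either feature is present to a moderate degree, the standard errors of the heat slope and the interaction are too small.

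Under the assumed values, the interaction's error rate for hourly data is about 25% to 70%, with 75% at the most extreme setting. At 5 minutes it is roughly 73% to 89%. Daily means give about 5% with homogeneous slopes, 5% to 12% at slope SD 0.25 and 14% to 37% at slope SD 1.0. With equal slopes and independent residuals it stays at 5%. Where the trial falls in this range cannot be told from the article. The sample size of 63 per group reproduces and is not in question.

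**What to change.** Amend the Statistical methods section, before data are analysed, to:

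- name the analysis epoch (for example hourly means) and the level of the random intercepts;
- add a woman-level random slope for WBGT together with a serial correlation term (AR(1) or its continuous-time equivalent), or use woman-level robust standard errors, or a two-stage analysis of per-woman slopes;
- adjust for facility, if at all, only when estimating the heat main effect, and keep facility-by-heat fixed effects out of the model that tests intervention-by-heat, because they alias it;
- state that woman-level inference does not cover variation in the heat slope between facilities, so with four facilities the interaction and the arm effect are exploratory.

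If a full protocol or analysis plan already contains the first two items, the article's wording only needs to be brought into line with it. The cost is a few lines of text, more computing and wider confidence intervals. No new data and no change in sample size are needed.

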### Data safety and monitoring

Continuous data recordings in this study include maternal ECG, triaxial accelerometry data, CBT, as well as WBGT measurements, ambient temperature and humidity data. All physiological and environmental data will be continuously recorded over a seven-day study period and temporarily stored on the respective devices. Subsequently, the data will be pseudonymized, removing any personal identifiers, and securely exported to encrypted, password-protected study computers. In parallel, the datasets will be backed up to two encrypted external hard drives to ensure redundancy and data safety. Data will then be securely transferred to Martin-Luther-University local computers by the external hard drives. Analysis will only be conducted on secure study computers. There is no ancillary and post-trial care as no harm from the trial participation is expected. Yet, appointed principal investigators will have access to interim results and the decision-making competencies to terminate the trial.

### Auditing

To ensure high data quality and protocol adherence, regular internal audits will be conducted by a member of the study team who is not involved in day-to-day data collection. These audits will include random checks of data completeness, consistency, and accuracy in the electronic database, with particular focus on physiological variables (e.g., HR, HRV, CBT, accelerometry data). Additionally, quality checks will be performed for data collected with the sensors to detect potential signal loss, noise, device malfunction, or non-physiological spikes, ensuring that only valid and reliable measurements are included in the analyses. Following the first data-collection phase and throughout the data-collection process, feedback sessions will be held among all data collectors, on-site researchers, and implementers to inform subsequent data collections.

### Harms and benefits

The measurements conducted during this study are non-invasive, and according to the manufacturers, do not pose a risk when worn [49–51]. Participants may benefit from additional assessments of their well-being during pregnancy and can choose to be informed about any incidental findings. These findings may be similar to those typically detected during routine antenatal care, such as maternal or fetal tachycardia, fetal growth restriction, fetal malformations, elevated umbilical artery resistance, or hypertension.

### Dissemination policy

Results from Physio-HeMAB will be integrated into the parent HeMAB study to inform interest-holder engagement and guide gender-transformative approaches with women, community members, healthcare providers, and policymakers. Study findings will be disseminated through peer-reviewed scientific publications, policy briefs, and academic conferences.

## Discussion

Physio-HeMAB is a comprehensive, non-invasive, multi-level physiological assessment designed to capture the complex interplay between environmental heat exposure, maternal physiological responses, and fetal health during pregnancy. A key strength of the study is the integration of continuous environmental monitoring, wearable-based maternal physiological measurements, and fetal assessments within a single analytic framework. Conducting the study within the Navrongo HDSS enables data collection under real-world living and working conditions, enhancing ecological validity and policy relevance. As a sub-study embedded within the larger HeMAB parent trial, Physio-HeMAB leverages the cluster-randomized implementation of a gender-transformative heat adaptation strategy to compare physiological responses between exposed and unexposed participants. This design strengthens the study’s relevance for adaptation policy by linking physiological evidence to a real-world public health intervention. Importantly, the study addresses a critical evidence gap, as most existing heat-related interventions and early warning systems are not tailored to pregnant women, and physiological evaluations of adaptation strategies in this population remain scarce.

Limitations include that the seven-day monitoring period per participant may not fully capture longer-term variability in heat exposure, behavioral adaptation, or physiological responses. Operationally, Physio-HeMAB is the first study of its kind conducted in this specific setting and with pregnant women. As such, uncertainties remain regarding participant retention, data completeness, inter-individual variability, and the performance of the multiple wearables and environmental sensors under field conditions. To address these challenges, the study deliberately enrolls a larger sample than required for the primary outcome, implements retention-enhancing procedures, and applies rigorous data quality control protocols.

Physio-HeMAB is designed to generate valuable methodological and physiological insights. By linking individual-level physiological responses to environmental heat exposure and adaptation strategies, the study supports the evidence base for the development of context-specific, gender-responsive, and scalable public health interventions aimed at protecting maternal and fetal health in a warming climate.

## Data Availability

No datasets were generated or analysed during the current study.

## Abbreviations

ANC: Antenatal care
ANS: Autonomic nervous system
BMI: Body mass index
bpm: Beats per minute
CBT: Core body temperature
ECG: Electrocardiography
GDPR: General data protection regulation
GLOHRA: German Alliance for Global Health Research
HC: Health center
HF: Health facility
HDSS: Health and demographic surveillance system
HeMAB: Healthy Mamas and Babies
HR: Heart rate
HRV: Heat rate variability
LMM: Linear mixed effects models
NHRC: Navrongo Health Research Center
SSA: Sub-Sahara Africa
UER: Upper East Region
UTCI: Universal Thermal Climate Index
WBGT: Wet-Bulb Globe Temperature
